### Outcomes and variables

The primary outcome of the trial is blood pressure control rate, which is the proportion of patients whose blood pressure is maintained within the target range. According to the National Basic Public Health Service Specification (Third Edition) [15], blood pressure should be controlled below 140/90 mmHg for individuals aged 35–65 years, and below 150/90 mmHg for those aged 65 years and above. Secondary outcomes: (1) standardized management rate: Calculated as the proportion of patients in the intervention and control groups who receive management in accordance with the National Basic Public Health Service Specification (Third Edition) [15], to evaluate the impact of the system on the standardization of hypertension management; (2) blood pressure measurement completion rate: The number of blood pressure measurements completed per patient compared to the expected quarterly measurements; (3) Referral rates: The number of patients referred to higher-level hospitals due to refractory or secondary hypertension, and the proportion of referred patients whose blood pressure stabilizes upon return; (4) Biochemical indicators: Changes in lipid profiles and other relevant biomarkers.

In addition, exploratory outcomes are economic evaluation(cost-effectiveness: analysis of system deployment costs versus improvements in hypertension control and reduced referrals; performance incentives: correlation between system-generated data and family doctor contract fulfillment metrics for incentive allocation), patient satisfaction (the subjective experiences and perceived effects), implementation barriers (engage professionals in focus groups and interviews to examine implementation barriers and improvement opportunities from the service providers’ perspective).

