### Statistical analysis

Statistical analysis will be performed using SPSS 27.0. Normality of continuous variables (e.g., blood pressure values, biochemical indicators) will be assessed using Shapiro-Wilk tests. Normally distributed data will be presented as mean ± standard deviation (x̄ ± s) and analyzed with independent t-tests for between-group comparisons (intervention vs. control) and paired t-tests for within-group changes (baseline vs. follow-up). Non-normally distributed data will be reported as median (interquartile range) and analyzed using Mann-Whitney U test. Categorical variables will be expressed as counts (%) and compared via the chi-square test. A two-sided p-value < 0.05 will indicate statistical significance.

Intention-to-treat analysis will be prioritized [19], with multiple imputation for missing data. Subgroup analyses will be performed for age, hypertension severity, and comorbidity status. In addition, insights on implementation barriers and improvement strategies derived from focus groups and interviews with healthcare professionals will be systematically analyzed using thematic analysis.

The economic evaluation is integrated into the quasi-experimental trial design, comparing the IoT-based hypertension surveillance system (intervention group, IG) with standard care (control group, CG). Costs and outcomes are assessed over a 12-month period to determine incremental cost-effectiveness. The analytical method is Incremental Cost-Effectiveness Ratio (ICER) [20], which is calculated using the following method. Where: ΔC = Change in mean costs (intervention vs. control). ΔE = Change in mean effectiveness (e.g., blood pressure control rate). Bootstrap simulation with 1,000 replications will be conducted to generate ICER distributions, plotted graphically on cost-effectiveness planes.$$\:ICER=\frac{\left({\Delta\:}{C}_{IG}-{\Delta\:}{C}_{CG}\right)}{\left({\Delta\:}{E}_{IG}-{\Delta\:}{E}_{CG}\right)}$$

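### The plan ties 'changes' only to within-group tests; conclusions on change outcomes should rest on a stated between-group contrast that accounts for baseline

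*Protocol article*

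**What the plan says.** The Statistical analysis section of the protocol article names the variables first: "Normality of continuous variables (e.g., blood pressure values, biochemical indicators) will be assessed using Shapiro-Wilk tests". Normally distributed variables are then "analyzed with independent t-tests for between-group comparisons (intervention vs. control"), and the same sentence adds "paired t-tests for within-group changes (baseline vs. follow-up"). For the rest, "Non-normally distributed data will be reported as median (interquartile range) and analyzed using Mann-Whitney U test". One rule covers all of these tests: "A two-sided p-value < 0.05 will indicate statistical significance".

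Under Outcomes and variables, the fourth secondary outcome reads "Biochemical indicators: Changes in lipid profiles and other relevant biomarkers". The Objectives ask whether the intervention improves biomarker profiles such as lipids and glucose, within a study that compares it with usual care.

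Two other places bear on the point. The Discussion acknowledges that allocation was not randomised, because the system was already deployed at certain sites. The section on participants and recruitment says that controls are matched on age, sex and hypertension duration. Baseline blood pressure and biomarkers are not among the matching variables.

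**The concern.** The outcome is a change and the question is comparative, but the text links change only to a test that does not use the control group. The null hypothesis of the paired test is that the mean change over time in one group is zero. Season, regression to the mean, routine treatment changes and the attention that comes with quarterly follow-up can move both groups alike. With 1,000 patients per group, even a small shared movement will often be significant within the intervention group.

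The between-group test is planned, but its scale is not stated. Run on follow-up values alone, it does not test the outcome as defined. It also takes in any difference that existed between the sites at baseline. At stake is whether the biomarker result, and any result reported for blood pressure values, can be read as an effect of the system.

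**Working it through.** The protocol gives no figure to reproduce here: it states no SD, no baseline/follow-up correlation and no expected time trend. Those quantities are assumed below and varied.

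**Inputs from the protocol.** 1,000 per group and 15% attrition (Sample size calculation), so 1,000 × (1 − 0.15) = 850 analysed per group. Two-sided 0.05 (Statistical analysis).

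**Assumptions.** The intervention effect is zero. Both groups drift by the same amount d, in SDs of the change score, with d from 0 to 0.20.

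**1. Paired t-test in the intervention group.** The noncentrality is d × √n. For d = 0.10 and n = 850 it is 0.10 × 29.15 = 2.92. The critical value is about 1.96, so the rejection probability is about P(Z > 1.96 − 2.92) = P(Z > −0.95) ≈ 0.83. The exact noncentral-t results are:

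| Shared drift d (SD of change) | n = 850 | n = 1,000 |
|---|---|---|
| 0 | 5% | 5% |
| 0.05 | 31% | 35% |
| 0.10 | 83% | 88% |
| 0.15 | 99% | 99.7% |
| 0.20 | >99.9% | >99.9% |

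**2. Between-group t-test on change scores.** In 4,000 simulated trials per setting (850 per group, correlation 0.5, d = 0, 0.05, 0.10 and 0.20), it rejected in 5.1% to 5.2%. The shared drift cancels.

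**3. Significant in the intervention group but not in the control group.** In the same simulations this pattern arose in 22% of trials at d = 0.05 and 13% at d = 0.10, with no effect present. It is not a test of the difference between groups.

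**4. Between-group t-test on follow-up values.** With groups equal at baseline it also held its level, at 4.7% to 5.3%. That equality cannot be taken for granted here. Suppose a baseline gap leaves a difference g at follow-up, in SDs of the follow-up value, with no intervention effect. The noncentrality is g × √(n/2), and √(850/2) = 20.62. By normal approximation:

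- g = 0.05: 1.03, rejection about 18%
- g = 0.10: 2.06, rejection about 54%
- g = 0.20: 4.12, rejection about 98%

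These values of g are illustrative; the protocol gives no baseline biomarker data.

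**The case against.** The strongest reply is that the sentence containing the paired test first assigns the same variables an independent t-test of intervention against control. A contrast with standard care is therefore planned. Nothing confines that test to follow-up values; with the outcome defined as a change, running it on change scores is a natural reading. The overall design section also frames the study as a comparison of the two groups. All of this stands, and it rules out three stronger readings that a reader might infer.

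- **That the biomarker outcome has no between-group test, or that a within-group p-value will decide efficacy.** The first is contradicted by the text, and no sentence says the second. Nor does any sentence say that significance in one group only will be read as an effect.
- **That Mann-Whitney will be applied to baseline and follow-up values of the same patients.** The plain reading is that it replaces the independent t-test. What is true is that no paired rank test is named for the within-group comparison.
- **That 83% is the plan's error rate.** The paired test is correct for its own null hypothesis. The figure becomes an error rate only if rejection is taken as an intervention effect.

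A fuller analysis plan may also settle the scale of the between-group test. That does not remove the point: the article's own wording sets between-group comparisons against within-group changes, gives both the same significance rule, and does not mark the second as descriptive.

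**Conclusion.** The point holds in a limited form. The plan has a between-group test for biochemical indicators and blood pressure values, but it does not say that this test addresses change from baseline or adjusts for baseline. The one test it does link to change cannot answer the comparative question. Under an assumed shared drift of 0.1 SD and no effect, that test rejects in about 83% of trials at 850 per group, against about 5% for a between-group test on change. The range is 31% to above 99.9% for drifts of 0.05 to 0.20 SD. A test on follow-up values alone is the weaker choice, because the groups are non-randomised and not matched on the variables concerned.

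The size rests on assumed drifts, since the protocol gives none. One secondary outcome is affected, plus blood pressure values if they are reported. The primary outcome is a binary control rate compared by chi-square and is untouched. The correction should be made, but the point does not undermine the trial's main comparison.

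**What to change.** In the Statistical analysis section:

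1. State that conclusions on change outcomes (the fourth secondary outcome, and blood pressure values if reported) rest on the between-group difference in change from baseline, or on a baseline-adjusted between-group difference, with its 95% CI. Choose one of the two in advance, because they can differ when groups differ at baseline.
2. Report within-group changes descriptively, and say that they are not evidence of an intervention effect, including when one group's change is significant and the other's is not.
3. If a within-group test is kept for non-normal variables, name the Wilcoxon signed-rank test.

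This takes a few sentences and no new data, since baseline laboratory values and blood pressure are already collected. The small cost is that statements of significant improvement within a group are dropped. Neither contrast removes confounding by factors that make the two groups change at different rates, so the limitation stated in the Discussion remains.

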## Methods

### Overall study design and setting

This study is a pragmatic quasi-experimental trial aimed at evaluating the effectiveness and feasibility of an IoT-based hypertension monitoring and management system in primary care settings. The overall study design is described in Fig. 1. The study compares outcomes between an intervention group (IG) using the IoT system and a control group (CG) receiving standard care. Quantitative data will assess clinical outcomes including blood pressure control rates, standardized management rates, and healthcare utilization, while qualitative methods will examine user experiences and implementation barriers through surveys and interviews with patients and healthcare providers (Fig. 2).

The study is carried out in Liyuan Health Center and its affiliated community health service stations in Tongzhou District, Beijing, P.R. China. The research area covers a large population of hypertension patients. It serves a population of approximately 250,000 people in urban and suburban regions, where the hypertension prevalence reaches as high as 33.3% [3]. The intervention is deployed across five family doctor teams in Liyuan Community Health Center and Xiaogao Community Health Station. These sites represent typical primary care institutions in Beijing’s urban expansion areas, serving mixed populations of long-term residents and recent migrants. The center utilizes Beijing’s municipal health information platform (B/S architecture) and has pre-existing health huts with basic measurement capabilities. The new IoT system integrates with these platforms through application program interfaces (APls) [13], enabling real-time data transmission from 6 intelligent monitors to electronic health records.

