Patients in the intervention group can view their daily blood pressure conditions on the display. If there are any abnormalities, they can receive timely treatment. They can also print out the results, health education prescriptions, and blood pressure trend charts on-site. Managers can inquire about the number of people taking blood pressure measurements, the standardized management rate and the blood pressure control rate of each team in our hospital on a daily, monthly and quarterly basis. Once a month, the information is summarized, a team meeting is held to analyze the data collected by the system, statistics are analyzed and made public, the team is urged to strengthen the blood pressure management and strive to improve their own level, and the doctors are urged to refer patients affecting the control rate to the higher-level hospitals so as to form a good diagnosis and treatment pattern. The control group is managed in the traditional way. Patients only have their blood pressure measured in the health hut, and the data is not included in the new system for statistics. Management is carried out in accordance with the requirements of the “National Basic Public Health Service Specification (Third Edition) [15]”.

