### Sample size calculation

A formal power calculation was performed a priori using G*Power software (version 3.1.9.7) for the primary outcome: the between-group difference in blood pressure control rate.

The anticipated control rate in the control group (P₁) was conservatively estimated at 45%, informed by historical data from our health center and findings from literature on usual care in similar settings [16]. We hypothesized that the IoT-based intervention would yield a clinically meaningful absolute improvement of 10% points, raising the control rate in the intervention group (P₂) to 55%. This effect size is supported by a recent meta-analysis of mHealth interventions [16], which reported a significant absolute improvement yet considerable heterogeneity among studies.

Using a two-sided significance level (α) of 0.05 and a power (1-β) of 80%, the calculation indicated a minimum requirement of 350 participants per group (total *n* = 700). Accounting for an estimated 15% attrition rate, the sample size was adjusted to 412 per group (total *n* = 824).

However, considering that there are more than 80,000 hypertension patients in this region and approximately 20,000 hypertension patients who have signed contracts with family doctors in this community, in order to achieve better research results and based on the available research resources, it was finally decided to include 2,000 patients, with 1,000 patients in the intervention group and 1,000 patients in the control group. This larger sample size ensures robust power for the primary and all secondary outcomes, enables precise subgroup analyses, and provides high-quality, generalizable evidence essential for informing public health policy on chronic disease management.

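### Exposure is set by family doctor team and site, but the sample size and the planned tests treat the 2,000 patients as independent, so the robust-power claim is unsupported unless within-team correlation is near zero

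*Protocol article*

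**What the plan says.** All places are in the protocol article.

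- **Who gets the system** (Overall study design and setting): "The intervention is deployed across five family doctor teams in Liyuan Community Health Center and Xiaogao Community Health Station". Controls are patients of teams at other stations without the system; their number is not given. The Discussion attributes the non-randomized allocation to where the system was already installed.
- **What it acts on** (Study intervention): besides the machines and screens, results are summarised monthly, discussed in a team meeting and made public, and "the team is urged to strengthen the blood pressure management and strive to improve their own level". Managers can follow the control rate, which is the primary outcome, team by team.
- **Sample size** (Sample size calculation): a two-proportion calculation. The control rate "was conservatively estimated at 45"% and the intervention is assumed to raise it to 55%. "Using a two-sided significance level (α) of 0.05 and a power (1-β) of 80"%, "the calculation indicated a minimum requirement of 350 participants per group", or 412 after 15% attrition. The number was then set at 1,000 per group, with the statement: "This larger sample size ensures robust power for the primary and all secondary outcomes, enables precise subgroup analyses". No ICC or design effect appears.
- **Analysis** (Statistical analysis): "Categorical variables will be expressed as counts (%) and compared via the chi-square test". Continuous variables are compared by independent t-tests or Mann-Whitney tests. There is no term for team or site and no cluster-robust variance.

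**The concern.** Patients of one team share doctors, machines, prescribing habits and, in the intervention group, the monthly feedback. Their outcomes are therefore likely to be correlated. The chi-square, t and Mann-Whitney tests assume that they are not. If the correlation is positive, the standard error of the group difference is understated, confidence intervals are too narrow and a true null is rejected more often than 5% of the time. Recruiting more patients within the same teams reduces only the within-team part of the variance, so raising the number from 412 to 1,000 per group does not by itself secure power.

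The primary conclusion is at stake. The article says the findings are meant to inform public health policy, and a difference between a handful of teams could be read as an effect of the system.

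**Working it through.** **The plan's own figure.** For 45% versus 55%, two-sided α 0.05 and 80% power:

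n = [1.96·√(2·0.5·0.5) + 0.8416·√(2·0.45·0.55)]² / 0.10² = 391.3, so 392 per group.

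The stated 350 does not reproduce; it gives 75.5% power. The attrition step does: 350/0.85 = 412. This is a separate matter with no consequence at 1,000 per group if patients are independent, since power is then 99.4% (98.5% with 850 analysed). The question is what remains once independence is dropped.

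**Inputs.** From the article: 45% and 55%, 1,000 per group, five intervention teams. Assumed: equal teams, so m = 1,000/5 = 200; five control teams of the same size; ICC from 0.001 to 0.05.

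**Formulas.**
- Design effect: DEFF = 1 + (m − 1)·ICC
- Effective n per group: 1,000/DEFF
- SE = √(0.2475·DEFF₁/1,000 + 0.2475·DEFF₂/1,000), with 0.2475 = 0.45·0.55
- Power: noncentral t, df = number of teams − 2, noncentrality 0.10/SE
- Type I error of the unadjusted test: 2·[1 − Φ(1.96/√DEFF)]

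**Example, ICC 0.01.** DEFF = 1 + 199·0.01 = 2.99. Effective n = 1,000/2.99 = 334. SE = √(2·0.2475·2.99/1,000) = 0.0385. Noncentrality = 0.10/0.0385 = 2.60. With 8 df the critical value is 2.306 and power is 63%. Type I error = 2·[1 − Φ(1.96/1.729)] = 26%. The 95% half-width is 2.306·0.0385 = 8.9 points, against 4.4 points in the unadjusted analysis.

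**Five teams per arm:**

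| ICC | DEFF | Effective n per group | Power (t, 8 df) | Type I error, planned test |
|---|---|---|---|---|
| 0 | 1.00 | 1,000 | 99% (normal approximation) | 5% |
| 0.001 | 1.20 | 834 | 95% | 7% |
| 0.005 | 2.00 | 501 | 80% | 16% |
| 0.01 | 2.99 | 334 | 63% | 26% |
| 0.02 | 4.98 | 201 | 43% | 38% |
| 0.05 | 10.95 | 91 | 22% | 55% |

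Power drops below 80% at an ICC of about 0.005 (t) or 0.008 (normal approximation).

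**Sensitivity at ICC 0.01.**
- 10 control teams of 100: control DEFF = 1 + 99·0.01 = 1.99, SE 0.0351, 13 df; power 75%, type I error 21%.
- 20 control teams of 50: control DEFF 1.49, SE 0.0333, 23 df; power 82%, type I error 19%.
- 850 analysed per group, 5+5 teams: power 60%, type I error 23%.
- Site as the unit, two per arm (the control number is assumed): DEFF = 1 + 499·0.01 = 5.99; power 19% (t, 2 df) to 45% (normal approximation), type I error 42%.

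**The case against.** **The size is assumed.** This is the strongest objection, and it stands. The article gives no ICC, no number of control teams and no team sizes; it says 1,000 patients are drawn from five teams, not 200 from each. A reader might infer that the power claim is simply false and that type I error is far above 5%. The document does not support that as a flat statement: at ICC 0.001 power is 95% and type I error 7%. Nor does a very small correlation always dominate the variance. The between-team part exceeds the within-team part only when 199·ICC > 1, that is, ICC above about 0.005. Likewise, adding patients to the same teams stops helping much only at larger ICCs.

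**More control teams would help.** True, as the sensitivity figures show, but the five intervention teams remain a limit: even with 20 control teams the type I error at ICC 0.01 is 19%.

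**An unseen analysis plan may specify a mixed model.** It may, but this document itself names the patient-level tests and makes the power claim, so both need correction here.

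**The design is already acknowledged as non-randomized.** The Discussion concedes selection bias from allocation by location. That concerns confounding, not variance. Matching on age, sex and hypertension duration, intention-to-treat analysis and multiple imputation do not remove within-team correlation either.

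**Conclusion.** The point holds in conditional form. The direction does not depend on the assumptions: any positive within-team correlation makes the planned p-values too small. The statement about robust power for all outcomes and precise subgroup analyses is unsupported unless the ICC is near zero. With five equal teams per arm, roughly 0.005 is where power for the primary outcome falls to 80% and type I error reaches about 16%.

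Confidence is high that clustering is ignored, and lower for any single percentage, because the ICC, the number of control teams and equal team sizes are all assumed. It should be corrected before analysis because it bears on the primary conclusion and the correction is cheap.

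**What to change.** 1. **Primary analysis.** In Statistical analysis, replace the chi-square test for the primary outcome with a mixed-effects logistic model with a random intercept for family doctor team and small-sample degrees of freedom, or with a team-level summary analysis. Adjust for the matching variables: age, sex and hypertension duration. Use the corresponding linear mixed model for continuous outcomes.
2. **Power statement.** In Sample size calculation, replace the sentence on robust power and precise subgroup analyses with power over ICCs from 0.001 to 0.05, using the actual number of control teams.
3. **Control sampling.** If recruitment allows, spread the 1,000 controls over as many control teams as exist, within the planned matching.
4. **Limitation.** State in the Discussion that, with the system at only two sites, site-level correlation and confounding cannot be separated from the intervention. A random intercept for team does not cure this, and intervals may still be too narrow.

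**Cost.** No extra patients. Patients are selected through their contracted team, so team membership should be available. The price is wider confidence intervals, a less favourable power statement and, if item 3 is adopted, a small change to control sampling.

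### The primary comparison is an unadjusted chi-square test under multiple imputation, which gives no estimate and standard error to pool; an adjusted risk difference pooled by Rubin's rules would serve better

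*Protocol article*

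**What the plan says.** All references are to the protocol article.

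- **Primary outcome** (Outcomes and variables, opening sentence): "The primary outcome of the trial is blood pressure control rate, which is the proportion of patients whose blood pressure is maintained within the target". For each patient this is a yes/no variable.
- **Test for it** (Statistical analysis): "Categorical variables will be expressed as counts (%) and compared via the chi-square test". No covariates are mentioned.
- **Continuous outcomes** (same section): t-tests if normally distributed. Otherwise: "Non-normally distributed data will be reported as median (interquartile range) and analyzed using Mann-Whitney U test".
- **Missing data** (same section): "Intention-to-treat analysis will be prioritized [19], with multiple imputation for missing data".
- **Quantity used for power** (Sample size calculation): "the between-group difference in blood pressure control rate", taken as 45% against 55%, two-sided 5%, 80% power. The attrition allowance is 15%.
- **Covariates available**: controls are matched to the intervention group on age, sex and hypertension duration (Participants, selection criteria and recruitment). Blood pressure and hypertension duration are recorded at baseline, with age and sex (Study conduct).
- **Allocation** (Discussion): the article acknowledges that allocation is not randomized and that confounding may remain after matching.

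**The concern.** Multiple imputation produces several completed data sets. Rubin's rules combine one estimate and its variance from each into a single estimate, standard error and p-value. A chi-square or Mann-Whitney test, as named, returns a statistic and a p-value, so an analyst who follows the section literally ends with several p-values for the primary outcome and no estimate to pool. The t-test does not have this problem, because it rests on a mean difference with a standard error.

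Two things are at stake. First, if the results were merged by a shortcut that treats imputed values as observed, the primary p-value could lose its 5% error rate. Second, an unadjusted test is a weak choice for the main comparison in a non-randomized trial that already collects the main prognostic variables. It uses none of them, and by itself gives neither an effect size nor a confidence interval.

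**Working it through.** **Inputs from the article.** 1,000 patients per arm; control rate 45% in the control group and 55% hoped for; two-sided alpha 0.05; 15% attrition.

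**Assumptions, because the article gives no figure.** m = 5 or 20 imputations; outcomes missing completely at random; 5%, 15% or 30% missing in each arm; independent patients; imputation within arm (Beta draw of the rate, then binomial draws).

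**The plan's own figure.** The usual formula gives n = [1.96√(2 × 0.5 × 0.5) + 0.842√(0.45 × 0.55 + 0.55 × 0.45)]² / 0.10² = (1.386 + 0.592)² / 0.01, or 392 per group against the stated 350. The attrition step does reproduce: 350 / 0.85 = 411.8, so 412. The gap between 350 and 392 is a separate matter and does not affect this point, since 1,000 per arm are enrolled. With 850 per arm observed, power is Φ[(0.10 − 1.96√(0.5/850)) / √(0.495/850)] = Φ(2.17) = 98.5%.

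**Valid ways to combine.**

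1. Rubin's rules on the risk difference. With mean estimate Q, mean within-set variance U and between-set variance B, the total variance is T = U + (1 + 1/m)B. Refer Q/√T to a t distribution with (m − 1)(1 + 1/r)² degrees of freedom, where r = (1 + 1/m)B/U.
2. The D2 rule on the chi-square statistics X. With r₂ = (1 + 1/m) × the variance of √X across sets, D2 = [mean X − ((m + 1)/(m − 1)) r₂] / (1 + r₂). Refer it to an F distribution with 1 and (m − 1)(1 + 1/r₂)² degrees of freedom.

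**Type I error**, from 40,000 simulated trials per setting with 45% in both arms. Cells show m = 5 / m = 20, in percent. The simulation error near 5% is √(0.05 × 0.95 / 40,000), about 0.1 points.

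| Method | 5% missing | 15% missing | 30% missing |
|---|---|---|---|
| Rubin, risk difference | 5.20 / 4.97 | 5.22 / 4.97 | 5.10 / 4.95 |
| D2, chi-square | 5.05 / 4.92 | 4.85 / 4.85 | 4.56 / 4.79 |
| One imputed set | 6.49 / 6.22 | 9.35 / 9.24 | 14.98 / 14.93 |
| Mean chi-square | 6.12 / 5.77 | 8.20 / 7.80 | 12.88 / 12.36 |
| Median p-value | 6.12 / 5.58 | 7.88 / 7.08 | 11.47 / 10.31 |
| Mean p-value | 5.46 / 5.01 | 5.97 / 5.14 | 6.94 / 5.46 |

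**Hand check of the single-set figure.** With a fraction f missing, the variance of the imputed arm mean, relative to the complete-data variance that the test assumes, is 1/(1 − f) + f²/(1 − f) + f = (1 + f)/(1 − f). At f = 0.15 this is 1.15/0.85 = 1.353, with square root 1.163. The true error is 2[1 − Φ(1.96/1.163)] = 2[1 − Φ(1.685)] = 9.2%. At f = 0.30 it is 1.30/0.70 = 1.857, square root 1.363, giving 2[1 − Φ(1.438)] = 15.0%. Both agree with the table.

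**Power** for 45% against 55%, 15% missing, m = 20: 98.4% for Rubin's rules and 98.4% for D2.

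**The case against.** The strongest case against has four parts.

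- **The test and the imputation can be combined.** A two-by-two chi-square test corresponds to a difference in proportions with a standard error, and the chi-square statistics can themselves be pooled. This stands. A reader might infer that the primary test has no valid combined result, but the table shows two routes that hold the error rate.
- **The inflation belongs to procedures that the article never proposes.** This also stands. A reader might infer that the primary p-value will miss its 5% level. Nothing in the article says that one set will be tested or statistics averaged, and averaging p-values stays fairly close to nominal.
- **The pooling rule, the number of imputations and the imputation model are details for an analysis plan that is not shown.** This stands too, and their absence is not the point made here. What remains is what the article does fix: a bare, unadjusted test as the comparison for the primary outcome, alongside imputation.
- **An effect measure is stated.** This stands in part. The sample size section names the difference in control rate, and the cost-effectiveness ratio uses a difference in effectiveness. The clinical comparison in the Statistical analysis section does not use it.

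Mann-Whitney bears only on non-normal continuous outcomes, which are secondary.

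**Conclusion.** The point holds as a poor choice of primary method that is worth changing. It does not show the planned test to be invalid. The named tests do not directly supply what multiple imputation pools, and the difference on which the trial was powered is not carried into the clinical analysis. Valid pooling is available, with type I error between 4.6% and 5.2% in every setting tried. The risk from improvised pooling at the plan's 15% attrition is about 9% for one imputed set and about 8% for the mean chi-square; this is conditional on a shortcut that the plan does not announce. These figures assume outcomes missing completely at random, independent patients and the chosen m. The simulation pooled an unadjusted risk difference. The case for adjustment rests on the non-randomized allocation and on the covariates already at hand, not on the simulation.

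**What to change.** Amend the Statistical analysis section as follows.

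- **Primary analysis:** a regression estimate of the risk difference (or odds ratio) in blood pressure control, intervention against control, adjusted for age, sex, hypertension duration and baseline blood pressure. Fit it in each imputed data set, pool by Rubin's rules and report it with a 95% confidence interval.
- **Continuous secondary outcomes:** linear models, pooled in the same way.
- **Chi-square and Mann-Whitney tests:** keep as descriptive or supportive.

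This ties the analysis to the quantity on which the trial was powered. It makes direct use of the imputation, can improve precision, and reduces confounding by the measured variables; unmeasured confounding remains. The cost is a few sentences of text and slightly more analysis work. All the covariates are already collected, so no extra data are needed.
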